### Secondary Outcomes:

- Asthma currently on treatment
- Death (any cause after randomisation)
- Respiratory outcomes (composite) – any respiratory diagnoses other than asthma including chronic lung disease
- Neurodevelopmental disability (composite) – any of:
  - visual impairment
  - hearing impairment
  - intellectual impairment
  - cerebral palsy
  - epilepsy
  - autism spectrum disorder (including Asperger's syndrome)
  - attention deficit disorder (ADD) or attention deficit hyperactivity disorder (ADHD)
- Cardiovascular outcomes (composite) – any cardiovascular diagnosis including hypertension, cardiomyopathies, arrhythmias, heart failure but excluding congenital heart disease
- Number of cardiovascular disease risk factors (composite categorised as 0, 1 or >1 risk factors) – any of:
  - high blood pressure
  - dyslipidaemia

- diabetes mellitus
- obesity/overweight
- Diabetes outcomes (composite) – any of prediabetes, diabetes mellitus, gestational diabetes mellitus
- Mental health outcomes (composite) – any mental health diagnosis including depression, bipolar affective disorder, schizophrenia, anxiety disorders, suicide/self-harm
- Bone health outcomes: any diagnoses related to bone disease
- Bone health outcomes: number of fractures
- General health outcomes: self-reported general health (reported health fair or poor)
- General health outcomes: functional difficulties (categorised as no disability / moderate or non-severe disabilities / severe disabilities)
- General health outcomes: oral health (reported oral health fair or poor or tooth extractions)

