| Cardiovascular outcomes (composite)

Defined as the presence of either of: 
 
1. Self-report of a cardiovascular condition.
 
2. Hospital admissions with diagnostic codes for a cardiovascular condition at any age.
 
3. Dispensing of a listed pharmaceutical for
 
 | Self-report questionnaire              | B1. Have you ever been told by a doctor that you have high blood pressure?
B5. Have you ever been told by a doctor that you have had a heart attack?
B12. Have you ever been told by a doctor that you have heart failure?
B13. Have you ever been told by a doctor that you have any other heart condition/s?

Free text response indicating a cardiovascular condition to one of the following questions: | May need to look at all of these as an adjudication committee |                                                                                                      |

| Study Outcome (definitions) | Priority Order for use of Data Sources | Details of data*:                                                                                                                                                                                                                                                                                                                                                                                                                                                                                                                                                                                                                                                                   | Criteria for adjudication (if applicable) | Comments/ Reference: |

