|-----------------------------|----------------------------------------|-------------------------------------------------------------------------------------------------------------------------------------------------------------------------------------------------------------------------------------------------------------------------------------------------------------------------------------------------------------------------------------------------------------------------------------------------------------------------------------------------------------------------------------------------------------------------------------------------------------------------------------------------------------------------------------|-------------------------------------------|----------------------|
| treatment of hypertension   |                                        | B41. Do you currently have any other major illnesses?
B42. Have you ever had any other major illnesses in the past?                                                                                                                                                                                                                                                                                                                                                                                                                                                                                                                                                              |                                           |                      |
|                             | NMDS admissions data                   | Admissions with the following ICD-10AM codes:
I151 Hypertension secondary to other renal disorders
I158 Other secondary hypertension
I420 Dilated cardiomyopathy
I451 Other and unspecified right bundle-branch block
I471 Supraventricular tachycardia
I490 Ventricular fibrillation and flutter
I495 Sick sinus syndrome
I499 Cardiac arrhythmia, unspecified
I500 Congestive heart failure
I517 Cardiomegaly
I518 Other ill-defined heart diseases
I822 Embolism and thrombosis of vena cava
I828 Embolism and thrombosis of other specified veins
I978 Other postprocedural disorders of circulatory system, not elsewhere classified |                                           |                      |

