|                                                      | NZ pharmaceuticals collection          | High blood pressure
Angiotensin converting enzyme (ACE) inhibitors
(i.e. Captopril, Cilazapril, Enalapril, Lisinopril, Perindopril, quinapril)
Angiotensin receptor blockers (ARBs) (i.e. Candesarten, Losarten, Irbesarten)
Beta blockers (Atenolol, bisoprolol, carvedilol, celiprolol, labetalol, metoprolol, propranolol, sotalol)
Diuretics (hydrochlorothiazide, bendroflumethiazide, chlorthalidone, indapamide)
Calcium channel blockers (amlodipine, diltiazem, felodipine, nifedipine)
Combination (inhibace plus, accuretic, Arrow-Losartan & Hydrochlorothiazide) |                                           |                      |
| Number of cardiovascular disease risk factors | Self-report questionnaire              | B1. Have you ever been told by a doctor that you have high blood pressure?                                                                                                                                                                                                                                                                                                                                                                                                                                                                                                                                                                          |                                           |                      |

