| 
(composite categorised as 0, 1 or >1 risk factors) – any of:
 
 
• high blood pressure
 
• dyslipidaemia
 
• diabetes mellitus (see following outcome)
 
• obesity/overweight
 
 
Defined as the presence of either of:
 
 
1. Self-report of a risk factor listed above.
 
2. Hospital admissions with diagnostic codes for a risk factor listed above.
 
3. Testsafe lab results of dyslipidaemia
 
4. Dispensing of a listed pharmaceutical for treatment of dyslipidaemia or hypertension
 
 |                                        | 
B3. Have you ever been told by a doctor that you have high blood cholesterol levels?
 
B18. Have you ever been told by a doctor that you have pre-diabetes or diabetes? (not including gestational diabetes)
 
BMI >25 as calculated using:
What is your current weight? (Q.F2)
What is your current height (Q.F3)
 |                                           |                      |
|                                                                                                                                                                                                                                                                                                                                                                                                                                                                                                                                                                                                                                                                                     | NMDS admissions data                   | 
Admissions with the following ICD-10AM codes:
 
Hypertension:
Essential hypertension; I110, I119
hypertensive heart disease; I120,
                                                                                                                                                                                  |                                           |                      |

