|-----------------------------|----------------------------------------|-------------------------------------------------------------------------------------------------------------------------------------------------------------------------------------------------------------------------------------------------------------------------------------------------------------------------------------------------------------------------------------------------------------------------------------------------------|-------------------------------------------------------------------------------------------------------------------------------------------------------------------------------------------------------------|----------------------|
|                             |                                        | E10 (Type 1 diabetes mellitus), E11 (Type 2 diabetes mellitus), E13 (Other diabetes mellitus), E14 (diabetes mellitus unspecified), O24.0 (pre-existing Type 1 diabetes mellitus during pregnancy), O24.1 (pre-existing type 2 diabetes mellitus), O24.2 (pre-existing malnutrition associated diabetes mellitus in pregnancy), O24.3 (pre-existing diabetes mellitus unspecified in pregnancy), O24.4 (Diabetes mellitus arising during pregnancy).. |                                                                                                                                                                                                             |                      |
|                             | NZ pharmaceuticals collection          | Prescription for any of the following*
Metformin (ie. Galvumet or Galvus (vildagliptin))
Insulin (rapid-acting: NovoRapid, Apidra, Apidra Solostar, Humalog) (short-acting: Actrapid, Humulin R)
(intermediate and long acting: isophane/Protophane, Humulin NPH, Lantus, Lantus Solostar, detemeir/Levemir)                                                                                                                          | If dispensed metformin and is male, then classify as diabetes mellitus. If dispensed metformin, is female and answers “no” to polycystic ovarian syndrome (PCOS) in questionnaire then classify as diabetes |                      |

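### The cardiovascular composite and the risk-factor count define hypertension inconsistently, accept dispensing of a listed drug as sufficient evidence, and omit Section 5's congenital-heart exclusion from the appendix, so some participants can be misclassified

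*SAP*

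**What the plan says.** Three features of the SAP bear on this point. The detailed definitions are in the outcome table of Appendix 15.2.

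- **Dispensing.** In the row for the number of cardiovascular disease risk factors, the fourth criterion is "Dispensing of a listed pharmaceutical for treatment of dyslipidaemia or hypertension". In the row for the cardiovascular composite, the third criterion begins "Dispensing of a listed pharmaceutical for" and goes on to name hypertension. In both rows any one criterion is enough. Both use the same list of drug names under a blood-pressure label, including the beta blockers "Atenolol, bisoprolol, carvedilol, celiprolol, labetalol, metoprolol, propranolol, sotalol". The composite's adjudication cell says that a committee might have to review these cases and states no trigger or criteria. The risk-factor row's cell is empty.
- **Congenital heart disease.** Section 5 ends its definition of the composite with "heart failure but excluding congenital heart disease". The outcome list at the start of Appendix 15.2 and the detailed row both omit the exclusion. The self-report items in that row include "B13. Have you ever been told by a doctor that you have any other heart condition/s", together with free text at B41 and B42.
- **Admission codes for hypertension.** The composite lists "I151 Hypertension secondary to other renal disorders" and I158. The risk-factor count lists "Essential hypertension; I110, I119", then I120, I129, I13x and I15x.

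**The concern.** Hypertension feeds two secondary outcomes (the composite and the risk-factor count) and two tertiary components (hypertension, and high blood pressure). A drug name does not give the reason for prescribing. The plan recognises this elsewhere. Asthma drugs, and ADHD and epilepsy drugs, count only with a repeat prescription. For metformin the rule is "If dispensed metformin and is male, then classify as diabetes mellitus", while in women the polycystic-ovary answer decides between classification and adjudication. The blood-pressure drugs have no comparable guard.

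The study hypothesis is that repeat corticosteroids have no long-term adverse effect. If false-positive cases arise equally in both groups, they pull a relative risk towards 1, the direction that favours that hypothesis. They also inflate the reported prevalence.

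The other two features are inconsistencies within the plan. One secondary outcome has two current definitions that differ on congenital disease, and one condition has two admission-code lists.

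**Working it through.** **Step 1: the dispensing rule beside the plan's other drug rules (Appendix 15.2).**

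| Outcome | Repeat prescription | Check for another indication | Adjudication |
|---|---|---|---|
| Any asthma | yes | no | yes, if self-report says no and one other source says yes |
| ADHD / epilepsy drugs | yes, within 2 years | no | none stated |
| Diabetes (metformin) | none stated | yes (polycystic ovary question, women) | yes |
| Mental health drugs | none stated | no | none stated |
| Hypertension, composite | none stated | no | possible, no criteria |
| Hypertension, risk-factor count | none stated | no | none |

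The composite also has arrhythmias, cardiomyopathies and heart failure as components. A participant dispensed a listed drug for one of those is correctly a composite case. The same dispensing also makes that person a case of the separate hypertension component and adds one to the risk-factor count.

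**Step 2: the congenital exclusion.** It is present in Section 5 and absent from both the appendix list and the detailed row. The composite's admission codes include no congenital heart code, so the admissions route already respects Section 5. The open routes are B13 and the free text at B41 and B42.

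**Step 3: the code lists.** The composite has {I151, I158}. The risk-factor count has {essential hypertension, I110, I119, I120, I129, all I13, all I15}. I151 and I158 both fall within I15x, so the first set is a strict subset of the second. Question B1 and the drug list are common to both outcomes. The outcomes therefore disagree only for someone who was admitted with a hypertension code outside I151 and I158, who has no yes at B1 and no listed drug, and who has no other qualifying cardiovascular evidence. Consenting participants who did not complete the questionnaire, a group Section 5 provides for, have no B1 answer.

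**Step 4: possible size, hypertension component only.** The SAP gives no figure to reproduce: it states neither the prevalence of hypertension nor how often a listed drug is dispensed for another reason. The values below are assumptions: true placebo prevalence p of 2%, 5% or 10%; true relative risk 2.0; and a share f of 2% to 10% of non-hypertensive participants, the same in both groups, dispensed a listed drug for another reason.

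Observed rate = p + (1 − p)f. False share of placebo cases = (1 − p)f / observed rate.

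Example with p = 2%, f = 2%: placebo 0.02 + 0.98 × 0.02 = 0.0396; repeat group 0.04 + 0.96 × 0.02 = 0.0592; ratio 1.49; false share 0.0196 / 0.0396 = 49%.

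| p | observed RR, f = 2% | observed RR, f = 10% | false share of placebo cases |
|---|---|---|---|
| 2% | 1.49 | 1.15 | 49% to 83% |
| 5% | 1.71 | 1.31 | 28% to 66% |
| 10% | 1.83 | 1.47 | 15% to 47% |

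Applying placebo prevalence to all 214 consenting participants, false positives number from 214 × 0.90 × 0.02 ≈ 4 to 214 × 0.98 × 0.10 ≈ 21.

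**The case against.** - **Expert review is foreseen.** Section 9 describes expert clinical synthesis of administrative and self-reported data, and the composite row names a committee. This stands in part: a check is contemplated for the composite. But no criteria are fixed, and the risk-factor row has no adjudication at all.
- **A repeat prescription is not a plan-wide rule.** Correct: the diabetes and mental-health rows state none either. The point is the lack of any guard for drugs with more than one use, not departure from a universal standard. A repeat dispensing does not establish indication in any case.
- **The two mismatches are narrow.** Correct: one acts only through self-report and the other only through admissions. Both are still internal inconsistencies that are easily removed.
- **The comparison has little power anyway.** With 107 per group (an equal split is assumed), a two-sided 5% test and no allowance for clustering, 2% against 4% has 13.5% power with perfect classification and 9.7% to 5.9% with the false positives assumed above. This limits the consequence for the test, but not for the reported prevalence or the clarity of the definitions.

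A reader might infer that the cardiovascular outcomes are in fact misclassified and that most recorded hypertension is false. The documents do not support that. The false share runs from 15% to 83% purely on assumed inputs. The calculation does not carry over to either secondary outcome: the composite adds other cardiac diagnoses, and the count adds BMI, dyslipidaemia and diabetes. The pull towards 1 requires equal error in both groups, which the SAP cannot establish.

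**Conclusion.** The point holds as a problem of definition. As written, the rules can count a drug given for another reason as hypertension, admit through self-report a condition that Section 5 excludes, and miss through admissions an essential-hypertension case in a composite that names hypertension as a component. These conclusions rest on the text alone.

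The amount of misclassification cannot be estimated from the SAP. That a listed drug may be given for something other than blood pressure is general clinical knowledge, and its frequency in this cohort is not stated. An observed relative risk of 1.83 to 1.15 for a true 2.0 illustrates the hypertension component only, under the assumptions given. The primary outcome, asthma, is unaffected. The repair is worthwhile because it is specific and cheap, not because a material bias has been shown.

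**What to change.** 1. Use one hypertension admission-code list, the broader risk-factor list, in both outcomes.
2. Restore the congenital exclusion in the appendix list and in the detailed row. Screen answers to B13, B41 and B42 for congenital heart disease, and state what happens when B13 is yes but no condition is named.
3. Where dispensing is the only evidence of hypertension, require a repeat dispensing as a minimum and send the case to adjudication blinded to treatment group, with the same written criteria for both outcomes. Cover participants who answered no to B1 and those with no questionnaire.
4. Date and label the change. The first addendum brought dispensing into the composite's hypertension definition, and it removed the stroke item so that the definition would agree with Section 5, but it left the congenital mismatch. The second addendum records that all analyses were complete before unblinding. A change now should therefore be a dated, labelled addendum, or a sensitivity analysis reported beside the definitions as they stand.

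The cost is appendix wording, a few adjudications and a re-run for two secondary outcomes and their components. The stricter dispensing rule leaves fewer events in outcomes that may already be sparse, although aligning the code lists could add a few to the composite.

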|                                                                                                                                                                                                                                                                                                                                                                                                                 | NMDS admissions data                   | Hospital admissions with a diagnosis of diabetes mellitus. This includes the following ICD 10 codes:                                                                                                                           |                                                                                                                                                                                                                                                                                                                                                                                                         |                      |

| Study Outcome (definitions) | Priority Order for use of Data Sources | Details of data*:                                                                                                                                                                                                                                                                                                                                                                                                                                     | Criteria for adjudication (if applicable)                                                                                                                                                                   | Comments/ Reference: |
|-----------------------------|----------------------------------------|-------------------------------------------------------------------------------------------------------------------------------------------------------------------------------------------------------------------------------------------------------------------------------------------------------------------------------------------------------------------------------------------------------------------------------------------------------|-------------------------------------------------------------------------------------------------------------------------------------------------------------------------------------------------------------|----------------------|
|                             |                                        | E10 (Type 1 diabetes mellitus), E11 (Type 2 diabetes mellitus), E13 (Other diabetes mellitus), E14 (diabetes mellitus unspecified), O24.0 (pre-existing Type 1 diabetes mellitus during pregnancy), O24.1 (pre-existing type 2 diabetes mellitus), O24.2 (pre-existing malnutrition associated diabetes mellitus in pregnancy), O24.3 (pre-existing diabetes mellitus unspecified in pregnancy), O24.4 (Diabetes mellitus arising during pregnancy).. |                                                                                                                                                                                                             |                      |
|                             | NZ pharmaceuticals collection          | Prescription for any of the following*
Metformin (ie. Galvumet or Galvus (vildagliptin))
Insulin (rapid-acting: NovoRapid, Apidra, Apidra Solostar, Humalog) (short-acting: Actrapid, Humulin R)
(intermediate and long acting: isophane/Protophane, Humulin NPH, Lantus, Lantus Solostar, detemeir/Levemir)                                                                                                                          | If dispensed metformin and is male, then classify as diabetes mellitus. If dispensed metformin, is female and answers “no” to polycystic ovarian syndrome (PCOS) in questionnaire then classify as diabetes |                      |

| Study Outcome (definitions)                                                                                                                                                                                                                                | Priority Order for use of Data Sources | Details of data*:                                                                                                                                                                                                                                                                                                                      | Criteria for adjudication (if applicable)                                     | Comments/ Reference:                                                                                                                                                                                                                                                                                                                                                                                                                                                                                                                                                                                                                                                                                                                                                                                 |
|------------------------------------------------------------------------------------------------------------------------------------------------------------------------------------------------------------------------------------------------------------|----------------------------------------|----------------------------------------------------------------------------------------------------------------------------------------------------------------------------------------------------------------------------------------------------------------------------------------------------------------------------------------|-------------------------------------------------------------------------------|------------------------------------------------------------------------------------------------------------------------------------------------------------------------------------------------------------------------------------------------------------------------------------------------------------------------------------------------------------------------------------------------------------------------------------------------------------------------------------------------------------------------------------------------------------------------------------------------------------------------------------------------------------------------------------------------------------------------------------------------------------------------------------------------------|
|                                                                                                                                                                                                                                                            |                                        |                                                                                                                                                                                                                                                                                                                                        | mellitus. If “yes” or did not answer PCOS question, then will be adjudicated. |                                                                                                                                                                                                                                                                                                                                                                                                                                                                                                                                                                                                                                                                                                                                                                                                      |
|                                                                                                                                                                                                                                                            | Testsafe lab results                   | HbA1c results + dates
Glucose tests + dates
GTT results and tests                                                                                                                                                                                                                                                                |                                                                               | 
New Zealand Society for the Study of Diabetes 2021 definition of diabetes mellitus.
 
If symptomatic diagnosed by
 
 
1. HbA1c <math>\geq</math> 50 mmol/mol, or
 
2. Fasting glucose <math>\geq</math> 7 mmol/L or
 
3. Random glucose <math>\geq</math> 11.1 mmol/L.
 
 
If asymptomatic diagnosed by
 
 
1. Two abnormal tests [HbA1c (<math>\geq</math> 50 mmol/mol), or fasting glucose <math>\geq</math> 7 mmol/L, or random glucose <math>\geq</math> 11.1 mmol/L] either on same day or subsequent test without delay.
 
2. If OGTT
 
 
Fasting glucose <math>\geq</math> 7 mmol/L or 2 hour glucose is <math>\geq</math> 11.1 mmol/L.
 |
| 
Mental health outcomes (composite)
 
Defined as the presence of either of:
 
 
1. Self-report of a mental health diagnosis.
 
2. Hospital admission with a mental health diagnosis
 
 | Self-report questionnaire              | 
D5. Have you ever been told by a doctor that you have depression?
 
D7. Have you ever been told by a doctor that you have bipolar disorder, which is sometimes called manic depression?
 
D9. Have you ever been told by a doctor that you have anxiety disorder? This includes panic attacks, phobia, post-traumatic
 |                                                                               |                                                                                                                                                                                                                                                                                                                                                                                                                                                                                                                                                                                                                                                                                                                                                                                                      |

| Study Outcome (definitions)                                                                                              | Priority Order for use of Data Sources | Details of data*:                                                                                                                                                                                                                                                                                                                                                                                                                                                                                                                                    | Criteria for adjudication (if applicable) | Comments/ Reference: |
|--------------------------------------------------------------------------------------------------------------------------|----------------------------------------|------------------------------------------------------------------------------------------------------------------------------------------------------------------------------------------------------------------------------------------------------------------------------------------------------------------------------------------------------------------------------------------------------------------------------------------------------------------------------------------------------------------------------------------------------|-------------------------------------------|----------------------|
| 3. Prescription of pharmaceuticals for treatment of mental health diagnosis
4. ACC data relating to suicide/self-harm |                                        | stress disorder, and obsessive/compulsive disorder.

Free text response indicating a mental health diagnosis to one of the following questions:
B41. Do you currently have any other major illnesses?
B42. Have you ever had any other major illnesses in the past?                                                                                                                                                                                                                                                                      |                                           |                      |
|                                                                                                                          | NMDS admissions data                   | F320-F329: Depressive episode
F330-F339: Recurrent depressive disorder
F310-F319: Bipolar affective disorder
F400-F409: Phobic anxiety disorders
F410-F419: Other anxiety disorders
F10-F19: Mental and behavioural disorders due to psychoactive substance use.
F20-F29: Schizophrenia, schizotypal, delusional, and other non-mood psychotic disorders.
F30-F39: Mood (affective) disorders.
F40-F48: Anxiety, dissociative, stress-related, somatoform and other nonpsychotic mental disorders.
F50: eating disorders. |                                           |                      |

| Study Outcome (definitions) | Priority Order for use of Data Sources | Details of data*:                                                                                                                                                                                                                                                                                                                                                                                                                                                                                                                                                                                                              | Criteria for adjudication (if applicable) | Comments/ Reference:                                                                                                                                                                                                                                                                                                                                                                                                                                                                                          |
|-----------------------------|----------------------------------------|--------------------------------------------------------------------------------------------------------------------------------------------------------------------------------------------------------------------------------------------------------------------------------------------------------------------------------------------------------------------------------------------------------------------------------------------------------------------------------------------------------------------------------------------------------------------------------------------------------------------------------|-------------------------------------------|---------------------------------------------------------------------------------------------------------------------------------------------------------------------------------------------------------------------------------------------------------------------------------------------------------------------------------------------------------------------------------------------------------------------------------------------------------------------------------------------------------------|
